### Random Allocation

The included patients will be allocated to one of the 3 treatment options by stratified block randomization: (1) the control group (sodium fluoride varnish; Duraphat, Colgate), (2) experimental group I (4% TiF_4_), and (3) experimental group II (S-PRG resin coating; PRG Barrier Coat, Shofu). The randomization sequence will be generated using Microsoft Excel 365 (Microsoft Corp) by an examiner who will not be involved in any of the clinical trial phases. To ensure allocation concealment, the randomly generated sequence will be sealed in opaque envelopes that will be opened only after the child is ready to receive treatment. The randomization procedure will be done per block of 3 children with the same SCASS scores to guarantee similar scores among groups at baseline.

The analysis unit will be the child and will be considered one tooth per child. If more than one permanent first molar has the condition, all will undergo the same treatment so that there is no interference from different treatments and other factors such as saliva, and one tooth will be selected by a draw to be included in the data analysis. The order of treatment among affected teeth in a patient will also be defined by a draw.

### Treatment Protocol

All children will receive instructions on noncariogenic diet and oral hygiene. Furthermore, the participants will receive an oral hygiene kit with toothbrush and fluoride toothpaste (both Colgate-Palmolive Company). Immediately before treatment, a supervised toothbrushing will be performed with a fluoride-free toothpaste to standardize the treatment phase and to follow the instructions of the S-PRG resin manufacturer. The study risks for participants are minimal and related to the sensitivity due to MIH.

In the control and experimental I groups, the fluoride varnishes will be applied once per week for 4 consecutive weeks. For the experimental II group, the product will be applied the first week and the application will be simulated the following 3 weeks for patient blinding.

All children in the control and experimental I groups will be treated according to the same protocol:

Supervised toothbrushing with fluoride-free toothpaste.Cotton roll isolation of the area.Drying of the tooth using sterile gauze.Varnish application with microbrush according to the manufacturer’s instructions.Instruction of the patient not to eat or drink for 30 minutes and not to brush for at least four hours after application.Reapplication once per week for 3 weeks, following the described protocol.Follow-up.

For the experimental II group, the treatment protocol according to the manufacturer is as follows:

Supervised toothbrushing with fluoride-free toothpaste.Cotton roll isolation of the area.Drying of the tooth using sterile gauze.Material handling within 2 minutes after mixing.Application of a thin layer with the device provided by the manufacturer, then a 3-second wait.Light curing for 10 seconds.Instruct the patient to avoid colored drinks and food for 3 days.Application simulation the following 3 weeks (repeat steps 1-3).Follow-up.

### Sensitivity Assessment

Sensitivity will be assessed before and after treatment (for all groups) using three instruments: the Wong-Baker FACES Pain Rating Scale (WBFPS), SCASS, and FLACC (Face, Legs, Activity, Cry, Consolability) scale, as described below.

First, the researcher will ask whether the child feels any discomfort in his/her teeth. The researcher will also carefully explain that their WBFPS face choice should be related to the toothache and not the child’s mood at that moment. The child will then be shown the WBFPS, and the child will be guided to choose the most representative face.

Second, sensitivity will be clinically assessed by applying a 1-second air jet 1 centimeter from the buccal and occlusal surfaces of the tooth. The adjacent teeth will be protected with cotton rolls and the patient’s response to the stimulus will be evaluated according to the SCASS. The child's reaction will be recorded according to the codes described in Multimedia Appendix 1.

Third, the examiner will also record the patient's reaction using the FLACC scale (Multimedia Appendix 2). This scale has 5 categories and the responses to each one will be scored from 0 to 2. In each category, the numbers obtained will be summed to obtain the total pain score (0-10). Finally, the child will be asked about discomfort in their teeth again following the use of the air jet and the WBFPS will be applied again.

### Primary Outcome: Treatment Effectiveness

A single trained, calibrated, and blinded examiner (not involved in the treatment application) will assess the sensitivity effectiveness of treatment in all groups at different moments: (1) before the application of each material, (2) immediately after application or simulation, (3) one month after the last application/simulation, (4) two months after the last application/simulation, (5) four months after the last application/simulation, and (6) six months after the last application/simulation. For all evaluations, the WBFPS, SCASS, and FLACC scale will be used as previously described.

### Secondary Outcomes: Parental Satisfaction and Child Self-reported Discomfort

Parental satisfaction and child self-reported discomfort will be evaluated immediately after the fourth week of application or application simulation. Children and their guardians will be asked to rate their satisfaction with the treatment received as very satisfied, partially satisfied, neither satisfied nor dissatisfied, partially dissatisfied, or very dissatisfied. Furthermore, parents will be asked about the importance attributed to the treatment performed on their children (ie, how important it is to treat the tooth affected by MIH) through 5 questions. Concerning discomfort, the questionnaire will assess the child’s acceptability of the treatment, especially the taste of the material, burning sensation, appearance, and duration of the procedure. The questions will be asked by an examiner who did not participate in the treatment stage and is not aware of the type of treatment received by the patient.

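### Child-reported discomfort is asked only after session 4, which is a real application in the varnish arms but a simulation in the S-PRG arm, so the measurement differs by arm

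*Protocol article*

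**What the plan says.** The section on secondary outcomes gives one time for parental satisfaction and child discomfort: they "will be evaluated immediately after the fourth week of application or application simulation". The discomfort part covers the child's "acceptability of the treatment, especially the taste of the material, burning sensation, appearance, and duration of the procedure". No earlier administration is described. The interviewer took no part in treatment and does not know the allocation.

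Under Treatment Protocol, for the control and experimental I groups, "the fluoride varnishes will be applied once per week for 4 consecutive weeks". For experimental group II, "the product will be applied the first week and the application will be simulated the following 3 weeks for patient blinding". The step list for that group defines the simulated sessions: "Application simulation the following 3 weeks (repeat steps 1-3", that is, brushing, cotton rolls and drying with gauze. The steps left out include "Application of a thin layer with the device provided by the manufacturer, then a 3-second wait" and "Light curing for 10 seconds".

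The Data Analysis section enters discomfort, with the plaque and gingival indices, as an explanatory variable in a Poisson regression on the outcome. It names no between-group test for discomfort. Satisfaction is to be described only.

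**The concern.** The listed items are mostly properties of a product and of the procedure that delivers it. At the only time they are asked, two arms have just had that product and procedure and the third has not. A child in the S-PRG arm who is asked about taste or burning has to think back three weeks, past three visits at which nothing was applied, or answer about the visit just finished.

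The difference goes with the arm. Randomisation does not remove it, and neither does a blinded interviewer, because it comes from what the child experienced and when. It also cannot be repaired at the analysis stage, since a reading after the first session would never have been taken.

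At stake is a named secondary outcome. The Discussion says patient-centred outcomes matter for choosing between treatments. This questionnaire is also the only place where the article describes asking about a burning sensation, and one of the products is a varnish that the Discussion says is not yet available.

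**Working it through.** No design figure is in dispute here, and the sample size calculation plays no part. The check sets the treatment schedule beside the questionnaire schedule.

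**Inputs.** Session content for each arm is from Treatment Protocol, questionnaire timing and items from the secondary outcomes section, and group size (20 per arm) from the sample size section.

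| | NaF varnish | TiF4 varnish | S-PRG coating |
|---|---|---|---|
| Sessions with real material | 4 of 4 | 4 of 4 | 1 of 4 |
| Content of session 1 | product | product | product |
| Content of session 4 | product | product | steps 1-3 only |
| Last real exposure | week 4 | week 4 | week 1 |
| Children asked after a simulated session | 0 of 20 | 0 of 20 | 20 of 20 |

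**Recall gap.** Let g be the time from the fourth session to the questionnaire. The gap since last exposure is g in the varnish arms and g + (4 − 1) weeks = g + 3 weeks in the S-PRG arm. The difference is three weeks whatever g is, so the point does not depend on whether the questionnaire is given within minutes or later that week.

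**Item by item.**
- Taste and burning: nothing in the simulated session can produce either. If children forget, or answer about that day's visit, the S-PRG figure falls. The likely direction is understatement.
- Duration: the simulated session omits mixing, application, the 3-second wait and the 10-second cure, so it differs from the real one. The document gives no total session times, so the direction is less certain.
- Appearance: the coating may still be visible at week 4, so the argument is weaker.

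**Size.** Suppose a fraction r of the S-PRG children who felt burning in week 1 still report it after session 4, and no one reports it falsely. The S-PRG figure is then r times the true proportion. With r = 1 there is no understatement; with r = 2/3 it is one third too low; with r = 1/3 it is two thirds too low. These values of r are assumptions. The document gives neither r nor any expected rate of burning, so the size cannot be narrowed further.

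**Is it measured elsewhere?** The Wong-Baker, Schiff and FLACC assessments are made after each session, including the first. They address pain and discomfort in the teeth, not taste, procedure time or the burning item of this questionnaire.

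**Where it enters the results.** It enters any table of discomfort by arm, and the Poisson regression, whose discomfort variable has a measurement error that depends on arm.

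**The case against.** The strongest reply is that the questionnaire rates the whole four-week course at its end. The Discussion presents the need for only one application as an advantage of the S-PRG coating, so lower discomfort in that arm could be a real difference between regimens. This stands in part: a whole-course rating is legitimate, and a session-1 reading alone would miss discomfort that builds up over four varnish applications. It does not remove the three-week recall gap. The simulated visits also exist only for blinding, so a whole-course rating in that arm includes visits that are not part of the treatment.

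Second, no between-arm test of discomfort is stated. That is correct, and it limits the point to by-arm reporting and the regression term.

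Third, the questionnaire is not reproduced. Its wording may direct the child to the product rather than to the latest visit. That would make rating the simulation less likely but would still rely on recall.

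A reader might go further and infer that any arm difference in these items is uninterpretable, or that bias toward the S-PRG coating is established. The document supports neither. The whole-course reading keeps some meaning, the direction is probable only for taste and burning, and no figure in the document gives a size.

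**Conclusion.** The point holds as an arm-dependent measurement of a secondary outcome. The only stated reading of taste, burning and duration follows a real application in both varnish arms. In the S-PRG arm it follows a simulation, three weeks after the sole exposure, and this applies to every child in that arm. S-PRG taste and burning are probably understated, by an unknown amount.

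This rests on two assumptions: that children aged 6-10 recall a brief sensation less fully after three weeks than just after it, and that the article lists every administration of the questionnaire. The primary outcome, the sample size and the treatment schedule are unaffected. It is a worthwhile, inexpensive improvement and does not threaten the trial's main conclusion.

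**What to change.** - Also give the discomfort items immediately after session 1 in all three arms, when every child has just received a real product. Use that reading for per-application comparisons between products.
- Keep the session-4 reading as the whole-course rating. Report it separately and state the three-week recall gap in the S-PRG arm.
- State which of the two readings enters the Poisson regression.
- Leave parental satisfaction at session 4.

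The cost is a few minutes per child at a visit already held, with the same blinded interviewer. No treatment, visit or sample size changes. Children already treated contribute only the session-4 reading. The Results section reports 6 treated, so if the change were made at that stage up to 60 − 6 = 54 of the planned 60 could give both readings.

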### Visible Plaque Index and Gingival Index

Considering that hypersensitivity can impact toothbrushing, the child’s oral hygiene condition will be evaluated using the visible plaque index (IPV) [29] and gingival index (GI) [30] at different times: (1) before the treatment, (2) before each material application/simulation, and (3) at each follow-up visit (1, 2, 4, and 6 months).

### Follow-up Examinations

Patients will be assessed regarding sensitivity 1, 2, 4, and 6 months after the treatment and will receive preventive instructions concerning diet and biofilm control. At the follow-up appointments, if a tooth displays posteruptive breakdown restricted to enamel, the patient will be kept in the study, but if the breakdown affects dentin (or in the case of a cavitated carious lesion), the patient will receive restorative treatment and be excluded from the study. If the patient has relapsed sensitivity, the initial treatment protocol will be maintained according to each group.

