## Introduction

Molar incisor hypomineralization (MIH) is a developmental defect of the enamel that affects one or more permanent molars, often associated with permanent incisors [1]. The affected teeth have lower mineralization, resulting in weaker enamel, which can undergo posteruptive breakdown [2,3]. The prevalence of hypersensitivity in MIH-affected teeth is around 34%, and some children might complain of spontaneous discomfort or pain triggered by thermal or mechanical stimuli [4].

Acute tooth sensitivity can occur when the dentist applies an air jet or performs clinical procedures. However, sensitivity can persist even after local anesthesia administration, resulting in anxiety and behavioral problems during dental treatment [5]. The cause of MIH sensitivity is not entirely clear [6]. One hypothesis is that repeated stimuli might cause a subclinical pulp inflammatory response due to the porosity of the enamel, which facilitates the penetration of bacteria in the dentinal tubules [6,7].

The management of MIH sensitivity represents a major challenge [1,4,7]. Several treatments are available, including the use of fluoride toothpaste, the use of oral care products containing casein phosphopeptides-amorphous calcium phosphate [8,9], and the application of topical sodium fluoride varnish [10-13] with or without laser therapy [14]. Sodium fluoride varnish retains the fluoride close to the teeth for a longer time, resulting in desensitization [15,16]. However, while the use of these agents is empirical, there are no long-term clinical trials with consistent results that evaluate their effectiveness.

The experimental 4% titanium tetrafluoride (TiF_4_) varnish is a promising material for decreasing sensitivity. Several in vitro and in situ studies have shown that TiF_4_ varnish has a greater remineralization effect and reduces enamel demineralization when compared to sodium fluoride varnish (5% NaF) [17,18]. Titanium tetrafluoride (TiF4) reacts with hydroxyapatite and induce a higher deposition of calcium fluoride, forming an acid-resistant layer [19,20].

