## Results

The children are currently being recruited. Thus far, 6 patients have been selected and treated, and they are now in the follow-up phase. At the 1-month follow-up, 1 participant was excluded since the tooth under evaluation was restored by a dentist in a private office. The first results are expected to be obtained in 2022.

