A previous study showed that patients benefit from MIH therapy as it reduces hypersensitivity, consequently allowing for proper oral hygiene and biofilm reduction [32]. However, that study compared the treatment effects of using fluoride varnish, fissure sealants, fillings, and stainless-steel crowns in teeth with different levels of MIH severity, and most of the teeth that received the varnish treatment had a mild level of MIH, without hypersensitivity. Contrarily, this study will assess only teeth without enamel loss and with hypersensitivity to evaluate the effect of different treatments on pain and consequently on biofilm accumulation and gingival health.

Secondary outcomes include parental satisfaction and child self-reported discomfort. Patient-centered outcomes are important for the selection of the best treatment. As the study will be carried out in children, obtaining the opinions of their family members is important and this will encourage greater involvement, commitment, and cooperation.

Finally, it is important to mention the limitations of the study. MIH is a dynamic condition that can get worse over time due to posteruptive breakdown, which can lead to dentinal exposure. In such a case, the hypersensitivity reported by the patient could be due to dentin exposure rather than the hypomineralized tissue. For that reason, teeth with dentin exposure in the follow-ups will be restored and excluded from the study. Additionally, although the short interval between visits lowers the risk of caries development, teeth that have cavitated caries will be restored and excluded from the study.

Thus, our study will emphasize the importance of treating teeth with MIH to relieve hypersensitivity and consequently improve children’s quality of life. If the results are satisfactory, this study will contribute significantly to the establishment of a treatment protocol for the control of sensitivity in teeth with MIH.

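### Children whose tooth breaks down into dentin, cavitates or is restored are excluded after randomisation, which leaves the arm comparison open to selection bias

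*Protocol article*

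**What the plan says.** Three places in the protocol article bear on this.

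- **Methods, Follow-up Examinations.** If breakdown reaches dentin, or a carious lesion cavitates, "the patient will receive restorative treatment and be excluded from the study". Two other events do not lead to exclusion: "if a tooth displays posteruptive breakdown restricted to enamel, the patient will be kept in the study", and "If the patient has relapsed sensitivity, the initial treatment protocol will be maintained according to each group".
- **Discussion, limitations paragraph.** The rule is repeated by tooth rather than by child: "teeth with dentin exposure in the follow-ups will be restored and excluded from the study", and "teeth that have cavitated caries will be restored and excluded from the study". The reason given is that in such a case "the hypersensitivity reported by the patient could be due to dentin exposure rather than the hypomineralized tissue".
- **Results.** At the 1-month visit, "1 participant was excluded since the tooth under evaluation was restored by a dentist in a private office". Follow-up Examinations does not list an outside restoration as a ground for exclusion.

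Data Analysis names a two-way repeated measures analysis of variance with a Tukey test. Nothing in the article says that excluded children stay in the analysis, that their earlier scores are used, or that exclusion counts as an unfavourable result.

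**The concern.** Exclusion after randomisation is harmless to the comparison only if it is unrelated to outcome or acts alike in every arm. The article gives grounds to doubt both.

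- **Link to outcome.** The Discussion says that exposed dentin can itself cause the sensitivity being measured.
- **Link to treatment.** The Introduction reports laboratory and in situ evidence that titanium tetrafluoride varnish protects enamel better than sodium fluoride varnish. The third arm is a light-cured coating. Different rates of breakdown or caries by arm are therefore plausible on the trial's own rationale.

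An arm that loses more of its structurally failing teeth would be judged on the children who did better. With 20 children per group, a few unequal exclusions matter, and the comparison at 4 and 6 months, where the long-term question is answered, is the most exposed.

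**Working it through.** **1. The plan's own figure.** Inputs from Selection of Participants and Sample Size Calculation: difference 1 SCASS point, SD 0.9, α 5%, power 80%, dropout 18%, 60 children (20 per group).

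One-way ANOVA with three groups and noncentrality λ = n·δ²/(2·SD²):

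- n = 16: λ = 16/1.62 = 9.88, power 0.782
- n = 17: λ = 17/1.62 = 10.49, power 0.809

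So 17 per group are needed, and 17 × 1.18 = 20.06, or 60 in total. The stated figure reproduces with that form of inflation. (Dividing instead, 17/0.82 = 20.7, gives 21 per group.) The dropout allowance covers loss of numbers. It does nothing about who is lost.

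**2. What selection could do.** The article gives no exclusion rates by arm and no correlation between exclusion and score, so everything in this step is assumed:

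- scores are normal with SD 0.9, and the true difference between two arms is 1.0;
- within each arm, the children with the highest latent risk are excluded, and that risk has correlation ρ with the score;
- a fraction p is excluded, 5% in the better arm and 15%, 25% or 31% in the worse arm. The pair 5% and 31% averages 18%, the plan's dropout allowance.

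The mean of the children who remain is lowered by SD·ρ·h(p), where h(p) = φ(z)/(1 − p), z is the (1 − p) normal quantile and φ is the normal density:

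- h(5%) = 0.1031/0.95 = 0.109
- h(15%) = 0.2332/0.85 = 0.274
- h(25%) = 0.3178/0.75 = 0.424
- h(31%) = 0.3528/0.69 = 0.511

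Shrinkage of the difference = 0.9 × ρ × [h(worse arm) − h(better arm)]. Example: ρ = 0.5, 25% against 5%: 0.9 × 0.5 × (0.424 − 0.109) = 0.14.

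| ρ | 5% vs 15% | 5% vs 25% | 5% vs 31% |
|---|---|---|---|
| 0 | 0 | 0 | 0 |
| 0.3 | 0.04 | 0.09 | 0.11 |
| 0.5 | 0.07 | 0.14 | 0.18 |
| 0.7 | 0.10 | 0.20 | 0.25 |

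A simulation of the same model gives the same values to within 0.01. With equal exclusion (5% in both arms, or 18% in both) the two h terms cancel and the shrinkage is about zero. If the better arm loses more children, the sign reverses and the difference is exaggerated.

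**3. Effect on power.** Holding 17 per group and SD 0.9, so that only the shrinkage acts, power falls from 0.81 to 0.77 at a shrinkage of 0.04 and to about 0.54 at 0.25.

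**4. Scope of the rule, side by side.** Follow-up Examinations speaks of a tooth and removes the patient. The Discussion removes teeth. The Results removed a participant for the tooth under evaluation, on a ground not listed in Methods. Random Allocation says that all affected molars are treated but one drawn tooth enters the analysis. The likely intention is that events on the drawn tooth count, but the wording does not fix this.

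**The case against.** The strongest defence has four parts.

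- **The exclusion has a reason.** Once dentin is exposed or the tooth is restored, a reading no longer measures sensitivity of hypomineralised enamel. That stands as a reason to treat later readings differently. It does not justify removing the child, and it does not undo the selection.
- **Most sensitivity failures stay in.** Relapsed sensitivity is not a ground for exclusion, and enamel-only breakdown is kept. This stands: a reader might infer that treatment failures in general leave the analysis, but only structural failures and restorations do. The Discussion adds that short visit intervals lower the caries risk, so numbers may be small.
- **Exclusion from the study may only mean that follow-up stops.** The article does not say that earlier scores are discarded, and a fuller analysis plan may settle this. That stands as a limit on the wording. The text as published still keeps no excluded child in the comparison.
- **No bias has been shown.** This also stands. A reader might infer that the comparison is biased, or that the worse arm would look better than the others. The documents give no rates by arm, equal exclusion under the same mechanism gives about none, and the illustration shows partial shrinkage, not reversal.

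Two further inferences should be resisted. One exclusion among six treated children (17%, exact 95% interval 0.4% to 64%) does not estimate how often the Methods rule will act, because that case was a private restoration with no breakdown or caries reported. Nor do the documents show that children with several affected molars are more likely to be dropped. That needs a literal reading of a tooth as any treated molar, which the drawn-tooth unit and the Results wording make unlikely.

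**Conclusion.** The point holds as a stated rule that opens the comparison to selection bias, not as a demonstrated bias. It rests on two links that the article itself supports: the excluding events are tied to sensitivity, and they may plausibly differ between agents. Size and direction depend on exclusion rates by arm, which are not given. The range of 0.04 to 0.25 points on a true difference of 1.0 belongs to the assumed 5% against 15% to 31% exclusion with ρ from 0.3 to 0.7. It should be read as an order of magnitude, not a prediction. The rule is worth changing because the repair is cheap and the planned analysis of variance cannot correct for selection if it runs only on the children who remain.

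**What to change.** Leave clinical care as planned and change the analysis rule.

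1. Replace exclusion from the study with a statement that the child stays in the analysis in the group to which he or she was randomised.
2. For the primary analysis, use every reading up to the event in a repeated-measures model that accepts incomplete series, for example a mixed model, and state its missing-at-random assumption. That assumption is itself open to doubt here, hence the next item.
3. Add a sensitivity analysis in which readings of the drawn tooth after the event are scored as unfavourable, for example SCASS 3. Label it as a composite treatment-failure strategy, since it answers a broader question than sensitivity alone.
4. Report dentin breakdown, caries and restoration by arm, with reasons.
5. Reconcile the three passages: state that only events on the drawn tooth count, say how outside restorations are handled, and apply the same rule to the child already excluded.

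The cost is revised wording and one extra analysis, with no added visits or children. The estimated benefit of an arm may turn out slightly less favourable.
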